#### Qualitative sample size

Following the 6-month assessment period (primary outcome collection), we will include a purposive sample of 20 participants per country, in individual qualitative interviews to discuss their experience of receiving the intervention. The sampling frame will be comprised of all patients randomised to the intervention arm and will explicitly include participants with positive or negative experiences of the intervention, those whose quality of life improved and those whose did not and those who frequently used or who did not receive the intervention during the testing period. Participant characteristics such as age, gender and clinical site (Pakistan) will also be considered. We will also aim to interview all seven clinicians in each country who delivered DIALOG+ to discuss their experiences of delivering the intervention.

#### Recruitment {15}

In order to ensure adequate participant enrolment, the teams have been actively engaged with the clinical sites. They have held strategy meetings with the management teams at each clinical site before initiation to ensure active involvement from admin and clinical staff. The research teams have set up a stepwise screening and enrolment process. They will actively search through electronic (where available) medical records or individual clinician caseloads to screen for eligible participants with the help of clinical and admin staff at each site. An on-site coordinator will assist with this process. Where patients do not have much time to spare, the research team will split up the consent and screening process to ensure that patients are not missed as a result of time shortage. The research team will also conduct home visits for patients who are unable to complete their assessments at the sites. Recruitment is anticipated to be completed within 6 months however, it is dependent on patient flow at each clinical site.

### Assignment of interventions: allocation

#### Sequence generation {16a}

Permuted blocked randomisation with block sizes of *m* = 4 and 2 will be used within each site. Randomisation will be carried out via an independent statistician via computer generated random numbers to determine allocation. Allocation to intervention and control will be in a ratio of 1:1.

#### Concealment mechanism {16b}

Allocation is only assigned after clusters are complete and all baseline data collected. Randomisation is conducted by independent team members within Queen Mary University of London. Participant allocation is provided only to the unblinded researcher and study coordinator. Allocation status will be saved in password protected electronic folders where they will be inaccessible to blinded researchers.

#### Implementation {16c}

Randomisation will take place after all patients have been enrolled, their baseline data collected and a clinician cluster formed. Randomisation will be conducted by an independent researcher based in the UK. The unblinded researcher will be responsible for informing participants of their allocation. Unblinded researchers/clinical site coordinators will train the clinical staff according to their allocation and schedule future appointments with patients and clinicians. Blinded researchers will not be present at the clinical site while the intervention period/appointment sessions are ongoing to avoid any unblinding.

### Assignment of interventions: blinding

#### Who will be blinded {17a}

Outcome assessors, data analysts and the overall study Principal Investigator will be blinded to the intervention allocation. All documentation revealing allocation will be securely stored and saved so it is inaccessible to blinded researchers. These researchers will have no contact with the participants enrolled and will not visit the clinical facilities when the intervention is taking place.

#### Procedure for unblinding if needed {17b}

In case there is any cause of harm to the participant involved, unblinding is permitted and will be dealt with according to specific safeguarding policies and SOPs in place.

### Data collection and management

#### Plans for assessment and collection of outcomes {18a}

All data is collected by researchers who have been trained in Good Clinical Practice as well as in the individual tools by specialists in their field. Training of clinical measures including BRPS and SANS were done by senior researchers and psychiatrists with previous experience of the measures. For the clinical measures, interrater reliability was established by independently rating videos using the measures and an independent researcher in the UK then calculated inter-rater reliability using the inter-rater correlation coefficient. A high correlation coefficient of over 85% was established and any discrepancies were discussed. Data will be collected on paper case report forms (CRFs). These will then be entered onto an electronic database (REDCap). The REDCap database was developed by the researchers and tested thoroughly at both sites. Data will be cleaned following local standard operating procedures (SOPs). Data collection forms can be available upon request from the authors.

#### Plans to promote participant retention and complete follow-up {18b}

Enrolment logs have been created and will be used to monitor the progress of all participants throughout the trial period until all data has been collected. Within the enrolment log, we monitor all meetings with participants including the date of randomisation, attendance at appointments and completion of each data collection point (baseline, 6 months and 12 months). Any withdrawals or deviation from protocols will be recorded and a note to file/withdrawal form will be added as required. Outcome data will be collected from all participants unless they have explicitly asked us not to contact them further. For participants who discontinue or deviate from intervention protocols, a purposive sample of qualitative interviews will be conducted at 6 months to understand any reasons for this. Sampling will be based on clinical site, gender and time of discontinuation/deviation.

Participants will receive reminder calls before each appointment and will be contacted in advance of any research assessments. Researchers schedule home visits to complete follow-up assessments where necessary. Participants will receive compensation for transport and the time taken for the data collection appointments (PKR 500 for screening, PKR 750 for complete assessment for patients and PKR 500 for caregivers in Pakistan and INR 300 for screening, INR 400 for complete assessments and INR 500 for caregivers in India).

#### Data management {19}

All data will be collected on paper based CRFs and safely stored within locked cabinets at the main trial site. Data from the CRFs will be quality checked by the local trial project manager (PM), as soon as possible. Any errors will be resolved with the individual who initially completed the CRF and verified against source documents where possible. All data will then be entered on electronic data collection tools designed on REDCap. The database has inbuilt validations to ensure data entry is as accurate as possible and during database development it went through multiple iterations of testing and feedback before finalisation to ensure smooth data entry operations. Data entered on REDCap will be periodically checked by the PM and against the source CRF to ensure there are no discrepancies. The team from the UK will also conduct regular monitoring visits and randomly check 10% of all the data collected and entered to ensure data quality is maintained. Data management procedures can be found in the ‘Document completion, Transport and Storage SOP’ and ‘Data Entry SOP’ created by each site. This is available upon request.

### Confidentiality {27}

#### Personal information

All data will be pseudonymised to maintain patient confidentiality. All participants will be assigned a participant ID number used for all data processing purposes. Patient identifiable data (participants’ names, contact details, sociodemographic data) and the list linking these data with the participant ID number will be stored on computers using a secure drive, within password-protected folders, which will only be accessible to the research team. All hard copies of data including socio-demographic forms, consent forms and patient receipts will be kept in lockable filing cabinets within premises of SCARF (India), JPMC (Pakistan), and KeH (Pakistan) or Interactive Research and Development (Pakistan) and only accessible by the research team.

To further protect confidentiality, we will:Ensure that participants understand during the informed consent process where interviews and focus groups might be audio-recorded, the purpose for the audio-recording, how the audio files will be stored, and who will have access to these files.Remind all participants that they do not have to answer any questions or make any personal disclosures if they do not wish to.Refrain from using participants’ names and the names of mental health services and during audio-recorded interviews. Participants will be reminded to refrain from using personal names or locations where possible at the start of the interview.Consent forms containing personal details of participants will be kept completely separate from the CRFs.

Where the researcher has concerns regarding the participant’s safety or the safety of others, through participant disclosures of thoughts/plans of harming themselves or others, then the researcher is obliged to break confidentiality and inform the relevant clinical teams, services and/or authorities. This will be made clear to the participant on the information sheet during the consent process to ensure their understanding.

All investigators and study staff will comply with the requirements of the Law 1581 (2012) and Decree 1377 (2013) and any other associated legislation of India and Pakistan regarding the collection, storage, processing, and disclosure of personal information and will uphold the law’s core principles throughout the study.

#### Audio recordings

The focus groups and individual interviews will be audio-recorded using an encrypted device with consent from participants. Audio recordings will be stored in password-protected folders on computers using a secure drive, which will only be accessible to the research team. The audio recordings will be destroyed immediately after transcription. All transcriptions will be completed by a professional transcription service. Prior to transcription, all identifiable information will be removed and/or replaced with pseudonymised labels.

#### Record retention and archiving

Research data will be retained and archived in accordance with the Research Governance Framework and IM&T Information and security policies. Records will be archived as per Queen Mary University of London procedures and kept for 20 years in the Trust Modern Records Centre. The PI ([name]) will be the custodian of the data.

The data will also be stored at the main study site in India (SCARF) where [name] will be custodian of the data and main study sites in Pakistan (JPMC and KeH) where [name] will be custodian of the data. This will be done according to the local regulations for data storage and protection.

Electronic data will be entered on a secure REDCap server in India and Pakistan and will be shared with the research team in the UK.

#### Plans for collection, laboratory evaluation and storage of biological specimens for genetic or molecular analysis in this trial/future use {33}

Not applicable as no samples collected.

### Statistical methods

#### Statistical methods for primary and secondary outcomes {20a}

A statistical analysis plan will be discussed and agreed with the local research team and the International Steering Committee (ISC) prior to data analysis. The local research team will take a leading role in the management and analysis of data. Data analysis will not be conducted prior to sign off and blinded members of the research team, including the statistician responsible for the analysis, will remain blinded until sign off has been obtained.

#### Quantitative data analysis

The number of screened participants, eligible participants, and of those who refused participation or were not approached will be recorded. The analysis will assess the number of intervention sessions received by participants, and we will collect data on drop-out (including reasons for drop-out if available) from treatment. The intervention topics discussed in meetings will be tabulated.

Descriptive statistics will be reported for socio-demographic data for all participants. Nominal and ordinal data will be presented as proportions (frequency), whereas continuous variables will be described utilising central tendency and variability measures. The latter will be selected according to distributions found (parametric or non-parametric), which will be evaluated through normality tests and histograms (probability functions). To assess the effectiveness of DIALOG+, mean and standard deviations (or median and interquartile range) over the three time points (baseline, 6 months and 12 months) will be calculated, and analysis will test the significance of the differences between the means (or other parameters) of outcomes measured. The primary outcome analysis will be the comparison of mean MANSA scores between treatment groups at 6 months follow-up using a mixed-effects model. This model will account for clustering by clinician, baseline values of the outcome (MANSA) and site (Pakistan) as covariates. A full analysis plan will be developed prior to data analysis, which will consider which covariates should be adjusted for in the model and methods for dealing with missing data.

The analysis will be conducted on an intention-to-treat basis, and every effort will be made to collect complete data. Patterns of missing data will be explored, and a strategy for dealing with missing values will be developed in the formal statistical analysis plan. Methods for dealing with missing data will depend on the extent, type and distribution of missingness.

#### Economic evaluation

The objective of the economic evaluation will be to inform decision-makers in India and Pakistan about the incremental cost and associated health outcomes of using DIALOG+ in the routine management of psychosis relative to the active control and from the perspective of the healthcare system. The supplementary objective of the economic evaluation will be to generate evidence on the costs of including DIALOG+ in the existing healthcare delivery systems in public and not-for-profit private sectors in India and in Pakistan.

The economic component will collect data on costs and health outcomes associated with the intervention and control arms. Costs will cover health sector costs and resources associated with providing the intervention as well as cost to the patient and their families for seeking care. Methods of micro costing will be used to determine the monetary value of the resources used for the management of psychosis with DIALOG+ and the active control. Healthcare cost will include time cost of healthcare providers, cost of capital resources and their maintenance and cost of supplies. A time and motion study will be conducted to estimate the resources use of the health facilities [28]. Purchase prices of all resources including supplies, instrument and furniture will be obtained from the respective health facilities where applicable, alternatively a market survey will be carried out. Data on resource use of the participants will be obtained from the customised CSRI to cover a retrospective period of 6 months prior to baseline and the two 6-month follow-up periods.

Health outcomes will be measured in quality-adjusted life years (QALYs). The European quality of life instrument EQ5D-5L will be used to capture health effects on patients, alongside the MANSA. Urdu and Tamil translation of EQ5D-5L will be obtained from the EUROQOL group. The EQ5D-5L tool will be administered at baseline, 6 months and 12 months follow-up. The valuation set of preference of the general population required to convert the EQ5D-5L to QALYs will be obtained from studies conducted in India [29] whereas the value set of EQ5D-5L for Pakistan is completed and ready for publication. The difference in outcomes, i.e. QALYs at the end and baseline of RCT, will demonstrate effectiveness for each arm of study and will result in the calculation of incremental health benefits of DIALOG+.

Incremental cost effectiveness ratios (ICERs) will be calculated as the ratio of difference in costs over difference in outcomes.

Uncertainty will arise in the estimates of cost, QALYs and ICERs from two sources (1) sampling and (2) methodological assumptions. Methods similar to those for the RCT will be used in the economic evaluation to deal with missing data or censored data. Skewness and correlation in cost and outcomes data will be treated with Bayesian or frequentist techniques. For Pakistani results, ICERS will be adjusted for clustering effect at facility level. Probabilistic one-way or two-way sensitivity analysis will be carried out as a robustness check for the uncertainty surrounding the estimated ICERs due to assumptions used while estimating costs and outcomes.

A health economic analysis plan will be developed and agreed with the local research team and signed off by the International Steering Committee (ISC) prior to data analysis.

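### The stated QALY measure, end minus baseline, is a change in utility without a time dimension, so the ICER built on it is not a cost per QALY

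*Protocol article*

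**What the plan says.** All of this is in the Economic evaluation section of the protocol article unless another section is named.

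- QALYs are the health outcome, and the instrument schedule is: "The EQ5D-5L tool will be administered at baseline, 6 months and 12 months follow-up".
- The value set is described as "The valuation set of preference of the general population required to convert the EQ5D-5L to QALYs". No step that multiplies utility by time is mentioned.
- The effect measure is then defined: "The difference in outcomes, i.e. QALYs at the end and baseline of RCT, will demonstrate effectiveness for each arm of study". The same sentence says that this "will result in the calculation of incremental health benefits of DIALOG"+.
- The ratio follows: "Incremental cost effectiveness ratios (ICERs) will be calculated as the ratio of difference in costs over difference in outcomes".
- Participants' resource use is collected for "a retrospective period of 6 months prior to baseline and the two 6-month follow-up periods", so costs after baseline run over 12 months.
- Detail is deferred: "A health economic analysis plan will be developed and agreed with the local research team", with steering committee sign-off before analysis.

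Separately, the Outcomes section lists the EQ-5D-5L among the secondary measures and plans baseline-adjusted comparisons of mean scores at both 6 and 12 months for all measures.

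**The concern.** A value set turns an EQ-5D-5L profile into a utility at one moment. A QALY is that utility multiplied by the time spent at it. There is therefore no QALY at baseline or at the end, only a utility, and subtracting one from the other gives a change in utility.

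Three things follow if the sentence is applied as written:

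- the effect has no time dimension, so the ratio is not a cost per QALY;
- the 6-month measurement has no weight in the effect, although it has the largest weight in a 12-month area under the curve;
- a cost accumulated over 12 months is divided by a difference between two time points.

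Cost-effectiveness is one of the three main aims in the Objectives section, and the economic evaluation is meant to inform decision-makers in both countries. A ratio with this denominator could not be compared with other cost-per-QALY figures.

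**Working it through.** The article gives no utility, QALY, cost or ICER figure, so there is nothing to reproduce. The check is algebraic, followed by assumed examples.

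**Inputs from the article.** EQ-5D-5L at 0, 6 and 12 months; effect per arm = end minus baseline; ICER = cost difference divided by outcome difference; costs over both halves of follow-up. I take the end to be the 12-month visit, the last assessment listed.

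**Notation.** u0, u6 and u12 are mean utilities in one arm. d6 and d12 are the between-arm differences at 6 and 12 months. Baselines are assumed equal.

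**Area under the curve, in years (trapezoidal rule).**

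QALY = 0.5·(u0 + u6)/2 + 0.5·(u6 + u12)/2 = 0.25·u0 + 0.5·u6 + 0.25·u12

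Incremental QALY = 0.5·d6 + 0.25·d12

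**Rule as written.**

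Effect per arm = u12 − u0, so the incremental effect = d12

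The weight on u6 is 0 here, against 0.5 in the area under the curve.

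**Effect on the ICER.** For the same cost difference,

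ICER(rule) / ICER(area) = (0.5·d6 + 0.25·d12) / d12 = 0.25 + 0.5·(d6/d12)

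This equals 1 only when d6 = 1.5·d12.

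**Examples.** The gains are assumptions, chosen to show the range.

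| d6 | d12 | Area: 0.5·d6 + 0.25·d12 | Rule: d12 | ICER under the rule |
|---|---|---|---|---|
| 0 | 0.05 | 0 + 0.0125 = 0.0125 | 0.05 | one quarter of the correct value |
| 0.05 | 0.10 | 0.025 + 0.025 = 0.050 | 0.100 | halved |
| 0.10 | 0.10 | 0.050 + 0.025 = 0.075 | 0.100 | 25% too low |
| 0.06 | 0.04 | 0.030 + 0.010 = 0.040 | 0.040 | unchanged |
| 0.10 | 0.05 | 0.050 + 0.0125 = 0.0625 | 0.050 | 25% too high |
| 0.10 | 0 | 0.050 + 0 = 0.050 | 0 | undefined |

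Gains that appear late or build steadily make DIALOG+ look more cost-effective than it is. Gains that fade by more than a third between 6 and 12 months (d12 below two thirds of d6) make it look less so.

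**The case against.** The strongest reply is that this is loose wording in a condensed article. The sentence gives no formula, and the QALY algorithm is what a health economic analysis plan normally settles. Three EQ-5D-5L visits are exactly what a trapezoidal QALY needs. A charitable reader could take the sentence to mean QALYs over follow-up relative to baseline. That would be harmless: subtracting one year at baseline utility gives −0.75·u0 + 0.5·u6 + 0.25·u12, and with equal baselines its between-arm difference is again 0.5·d6 + 0.25·d12.

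Part of this stands. The later plan may well specify the area under the curve, and the finding does not show that the eventual analysis will be wrong. But the article did not leave the point open. It states a two-point definition and carries it into the ICER, and nothing else in the section mentions time weighting. A later plan that used the area under the curve would depart from the published text, and one that followed the text would be invalid.

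Some stronger readings are tempting but unsupported:

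- *The 6-month EQ-5D-5L is thrown away.* No sentence says so. Its absence from the QALY follows by implication from the two-point definition, and the Outcomes section still compares 6-month scores.
- *The benefit is expected to peak at 6 months.* The Intervention description says only that sessions are monthly for 6 months and then discretionary. It does not predict when the effect is largest.
- *Any fading gain counts as zero.* Only one that has vanished completely by 12 months does. A gain of 0.10 falling to 0.05 counts as 0.050.
- *The ICER is wrong by a known amount or in a known direction.* Both depend on a utility profile that the document does not give.

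**Conclusion.** The point holds as a defect in the stated definition. As written, the effect measure is a 12-month change in utility and not a QALY, and it is the ICER denominator for a main aim.

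The algebra needs only the three visit times, the trapezoidal rule and equal baselines. The size does not follow from the document. In the assumed examples the ICER ranges from one quarter of its correct value to 25% too high, and it is undefined when the 12-month gain is zero. The two measures agree only when the 6-month gain is 1.5 times the 12-month gain.

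The primary outcome, sample size, randomisation and data collection are not affected. The correction should be made before the health economic analysis plan is signed off.

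**What to change.** Replace the sentence in the Economic evaluation section, and carry the replacement into the health economic analysis plan:

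*QALYs over 12 months are calculated for each patient as the area under the EQ-5D-5L utility curve (trapezoidal rule over baseline, 6 and 12 months); the incremental QALY is the between-arm difference adjusted for baseline utility.*

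It would also help to say that the value set converts EQ-5D-5L responses to utilities, and that QALYs come from the time-weighting step.

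The cost is a change of wording in two documents. All three measurements are already scheduled, so no visits, instruments or patients are added.

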### Trial design {8}

To test DIALOG+ within routine healthcare settings in India and Pakistan we are conducting a cluster RCT. The design of the cluster RCT was finalised after incorporating the results of a pilot study which informed local adaptation of the intervention.

The unit of analysis for the cluster RCT will be the mental health professionals, who will be recruited from outpatient clinics at three included clinical sites (two in Pakistan and one in India). The caseloads of the mental health professionals will be screened by researchers to identify potentially eligible patients. The clinician along with their enrolled patients will form individual clusters and will be allocated on a 1:1 basis to either the control (DIALOG scale) or the intervention arm (DIALOG+).

Assessors will be blinded to participant allocation for all data collection.

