## Methods: participants, interventions and outcomes

### Study setting {9}

The research will be conducted in two urban settings: one outpatient clinic in Chennai, India (Schizophrenia Research Foundation - SCARF), and two facility centres in Karachi, Pakistan—a public-sector tertiary hospital (Jinnah Postgraduate Medical Centre—JPMC) and an outpatient clinic at a private mental health hospital (Karwan-e-Hayat- KeH).

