### Sample size {14}

#### Quantitative sample size

In order to detect a medium effect size of 0.5, setting power at 90% for 5% significance, accounting for clustering based on an ICC of 0.002 (as observed within the DIALOG+ trial [15]), and applying a conservative design effect of 1.03, the total number of patients required in each country is 84 per group (*n* = 168 per country). After allowing for a drop-out rate of 20%, a total of 210 patients will need to be recruited to give the analysable sample of 168 or 84 per group. Therefore, 14 clinicians will need to be recruited in each country, with an average of 15 patients per clinician.

Clinicians of any background, including lay community workers will be eligible. Meetings held within each of the participating clinical services indicated that there were sufficient numbers of both clinicians and patients, with many outpatient clinics seeing 100+ patients with psychosis per day.

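### The economic evaluation names facility, in Pakistan only, as its clustering level, although the randomised clusters are clinicians in both countries

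*Protocol article*

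**What the plan says.** The Economic evaluation section of the protocol article makes one statement about clustering: "For Pakistani results, ICERS will be adjusted for clustering effect at facility level". It makes none for the Indian results and does not mention clinicians as clusters. It carries trial methods over to the economic analysis for missing and censored data only, and leaves further detail to a health economic analysis plan that the steering committee will sign off.

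Elsewhere the cluster is the clinician:

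- Trial design {8}: "The clinician along with their enrolled patients will form individual clusters and will be allocated on a 1:1 basis".
- Quantitative sample size: "Therefore, 14 clinicians will need to be recruited in each country, with an average of 15 patients per clinician".
- Quantitative data analysis, on the primary outcome: "This model will account for clustering by clinician". The same model has site (Pakistan) as a covariate.
- Sequence generation {16a}: "Permuted blocked randomisation with block sizes of *m* = 4 and 2 will be used within each site".

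Study setting {9} gives the number of facilities: "two facility centres in Karachi, Pakistan" and "one outpatient clinic in Chennai, India".

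**The concern.** Patients of one clinician share whatever that clinician does, and treatment is allocated by clinician. The variance of any between-arm difference therefore contains a between-clinician part. The economic section gives the role of cluster to the facility, which the primary model handles as a covariate, and does not mention the randomised unit.

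Similarity within clinician is plausible for costs. Provider time is a cost component, clinicians of any background including lay workers are eligible, and in months 6 to 12 use of the intervention is at the discretion of patient and clinician.

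Cost-effectiveness is one of the three main aims and is meant to inform decision-makers in both countries. An economic plan that follows this sentence could report incremental costs and QALYs with more certainty than the design supports, at a different level from the primary analysis of the same patients.

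**Working it through.** **1. Which unit the plan's own design effect uses.** Quantitative sample size gives an ICC of 0.002 from an earlier DIALOG+ trial, 210 patients and 14 clinicians per country, and a design effect of 1.03.

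- Cluster size: 210 / 14 = 15.
- Design effect: 1 + (m − 1) × ICC = 1 + 14 × 0.002 = 1.028, which rounds to the stated 1.03.

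The figure reproduces with the clinician as cluster, so the sample size and the primary model agree on the level.

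**2. What a facility adjustment can capture.** Pakistan has two facilities, so one degree of freedom between facilities, which is too few to estimate a clustering variance. India has one facility, so there is nothing to adjust for at that level. Each country still has 14 randomised clinicians. A facility term removes the mean difference between the two Karachi facilities and leaves the variation between clinicians within a facility untouched.

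**3. Size if clinician clustering is left out.** After the planned 20% drop-out, 168 / 14 = 12 patients per clinician are analysed. The omitted design effect is 1 + 11 × ICC, and the standard error is too small by 1 − 1/√(design effect). The protocol gives no ICC for costs or QALYs; all values below except 0.002 are assumptions, and 0.002 is itself only the sample-size value.

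| ICC | Design effect | Standard error too small by | Simulated coverage, facility term only | Simulated coverage, clinician level |
|---|---|---|---|---|
| 0.002 | 1.022 | 1.1% | 95.1% | 95.6% |
| 0.01 | 1.11 | 5.1% | 93.8% | 95.1% |
| 0.02 | 1.22 | 9.5% | 92.1% | 95.1% |
| 0.05 | 1.55 | 19.7% | 88.6% | 95.0% |
| 0.10 | 2.10 | 31.0% | 82.3% | 95.3% |

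The last two columns are coverage of a nominal 95% interval for a mean difference in a Pakistan-like layout. The simulation had 8,000 replicates, 2 facilities × 7 clinicians × 12 patients, 7 clinicians per arm, normal outcomes and equal cluster sizes. It compared patient-level regression with a fixed facility effect against analysis of clinician means with the same facility effect. The even split of clinicians between facilities is assumed. No cost data are given, so an ICER interval itself cannot be computed.

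**The case against.** Five points can be made for the plan.

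- **Silence is not exclusion.** The section names one adjustment and does not say it is the only one; the economic plan may add clinician clustering. This stands. A reader might infer that the protocol excludes clinician clustering, or has decided that India gets no adjustment, but the text says neither. It does state a level, though, and that level does not match the design. An economic plan that follows the sentence would inherit it.
- **It may be the site covariate, loosely worded.** Only Pakistan has more than one facility, and the primary model uses the same Pakistan-only form for its site term. This is probably how the sentence arose. On this reading a facility term is right to have, but it is mislabelled as clustering and the clinician term beside it is missing.
- **The estimator is not named.** Treating the two facilities as the clusters, with one degree of freedom, would give very wide or unusable intervals. Intervals that are too narrow follow only if facility enters as a covariate and clinician is left out. This stands and limits the conclusion.
- **The article uses the word site loosely,** for the three clinics in Trial design and for the two countries in the data collection and data availability text. It is therefore not certain that blocking was within facility. The finding does not need it: the randomised unit is the clinician either way.
- **The large percentages rest on assumed ICCs.** At the only documented value the effect is about 1%. This also stands.

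**Conclusion.** The stated clustering level for the ICERs contradicts the design. It names facility, in Pakistan only, where the randomised clusters are 14 clinicians in each country and the primary model treats them so. A facility adjustment cannot stand in for clinician clustering with two facilities in one country and one in the other.

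A reader might go further and infer that the ICER intervals will be too narrow. The protocol does not support that as a fact: no interval method is fixed, clinician clustering is unstated rather than ruled out, and no analysis has been done. The understatement is conditional on facility being the only adjustment and on the cost and QALY ICC. It is negligible at 0.002, about 10% of the standard error at an assumed 0.02, and about 20% to 31% at assumed values of 0.05 to 0.10.

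This should be fixed, but it is not critical: the primary outcome, its model, the sample size and the randomisation are unaffected.

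**What to change.** Replace the sentence in the Economic evaluation section, and carry the same text into the health economic analysis plan before sign-off:

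> In both countries, incremental costs, QALYs and ICER uncertainty will be estimated with clinician as the cluster (for example a bivariate multilevel model or a two-stage cluster bootstrap, with a small-sample correction for 14 clusters per country); in Pakistan, facility will be included as a fixed-effect covariate, as site is in the primary analysis.

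The cost is slightly more programming and somewhat wider intervals. For example, a t reference on 14 − 2 = 12 degrees of freedom replaces 1.96 by 2.18, which widens an interval by about 11% before any clustering (2.18 / 1.96 = 1.11). Design and data collection do not change.
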